## Methods

### Study design

The design is a randomised controlled feasibility trial (comparing a psychological decentering training to an active control programme) with school aged adolescents (aged 16–19 years). The study will run from December 2021 until July 2022, split into several cohorts. Self-rated inventories of training and mental health outcomes will be assessed at three time points: within 1 week prior to the start of programme (baseline); within the third week of training (mid-intervention); and 1 week after the programme has finished (postintervention).

### Participants and inclusion/exclusion criteria

Two groups of older adolescents (n=57 per group; age range=16–19 years) will be recruited from the UK and Ireland. Eligible participants must consent to completing (1) a 5-day ESM baseline assessment, (2) 5 weeks of the assigned training programme and (3) assessment measures at baseline, mid-intervention and post intervention. In exchange for their time, participants will be compensated with shopping vouchers worth (1) £100 pounds (for completing 5 weeks of training) and (2) £20 (as a bonus for completing all assessments). Eligible participants must also report a score of 16 or above on the Centre for Epidemiological Studies-Depression Scale (CES-D), based on standard CES-D cut-offs. Participants must also have access to a laptop/desktop computer and a personal smartphone device.

Participants will be excluded if they: (1) currently take part in a regular (once or more per week) yoga and/or mindfulness class/workshop, (2) have participated in prior formal meditation training or a mindfulness-based stress reduction course, (3) are currently experiencing chronic illness (eg, epilepsy, chronic pain, cancer), (4) lack fluency in English, (5) have a recent diagnosis of, and are currently receiving medical/psychological treatment for, a mental health condition including (but not limited to) anxiety disorder, major depressive disorder or a traumatic stress disorder and (6) have a diagnosis of a neurodevelopmental condition such as autism spectrum disorder or attention deficit/hyperactivity disorder. Both the decentering programme and active control programme require adolescents to be without severe hearing difficulties since both conditions require listening to audiotapes. As the control condition involves physical movement routines, it may not be appropriate for specific individuals, such as individuals with limited mobility. Any volunteer who meets the exclusion criteria will be accommodated as best as possible (eg, assignment to the most appropriate condition in the case of a physical disability) and their data will not be included in the analysis.

### Recruitment

Participants will be recruited from the general community through a combination of existing collaborations with schools in the UK and Ireland. We will also recruit UK and Irish volunteers via online research platforms (eg, Prolific; www.prolific.co) as well as extant panels of adolescent research volunteers via the MRC-Cognition and Brain Sciences Unit (University of Cambridge). Finally, and if necessary, we will also conduct a targeted recruitment campaign to recruit young people and schools using posters, pamphlets and online adverts on social media.

### Sample size

The primary training outcome is self-rated decentering and this will be assessed using both a popular inventory of decentering (Experiences Questionnaire; EQ^8^) and ESM items. There is no consensus on how to best conduct a statistical power analysis for ESM data. Power and sample calculations were therefore based on the effect of training condition on EQ scores. A power analysis calculated in G*Power indicated that a total sample size of 90 is powered at 80% to observe a significant effect of training condition (decentering vs control) on postintervention decentering with a medium effect size of f=0.3 (α=0.05) after adjusting for baseline EQ score. A medium effect size is plausible given that previous research reports a medium–large effect of extant psychological intervention on EQ scores. An attrition rate of around 20% is anticipated based on our previous research. Therefore, with 57 participants in each group, the current study is adequately powered to observe a medium to large effect of decentering training on our candidate training outcome measures and to determine the nature of this interaction. Regarding our secondary mental health outcomes (ie, anxiety, depression and psychological well-being), a sample size of 57 per group is consistent with our previous research to evaluate the impact of novel psychological interventions. That is, such group sizes can provide a reasonable range of point estimates of the effect on mental health outcome measures that are sufficient to guide later research; for example, 57 participants per group is powered at 88% to observe a significant (p<0.05) main effect of group (decentering vs active control) on baseline adjusted mental health outcomes with an effect size f=0.26.

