#### Statistical analysis

##### Self-rated and performance-based measures

The statistical analysis will be conducted by the trial statistician (PW) who will be blind to training condition. The analysis will be conducted on an intention-to-treat basis and a similar initial analysis is planned for (1) the primary training outcome (ie, self-rated EQ scores) and (2) secondary mental health outcomes (ie, CES-D, RCADS, STAXI-2, SDQ and WEMWBS). Analysis of covariance will be calculated to estimate the effect of training condition on outcome measures after adjusting for baseline performance and grouping stratification variables. This model will be calculated for our primary end-point, that is, post intervention (ie, postintervention outcome adjusted for baseline score). This model will additionally be calculated for our mid-intervention time point (ie, mid-intervention outcome adjusted for baseline score) and post intervention. There are no planned interim analyses. If a subset of items of a measure (<20% within-measure missing data), a total score will be calculated using the mean score across the non-missing items; an approach we have reported elsewhere (www.osf.io/d6y9q). Otherwise, the score for that measure will be noted as missing. We will assume that data will be missing at random and address this using standard imputation approaches in R (R Core Team, 2013).

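### The 88% power given for the mental health outcomes does not follow from its inputs: f=0.26 with 57 per group gives 79%, and about 69% after the plan's own 20% attrition

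*Protocol article*

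**What the plan says.** The Sample size section of the protocol article makes two power statements.

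- **Primary outcome (Experiences Questionnaire, EQ).** From G*Power, "a total sample size of 90 is powered at 80"% for f=0.3 at α=0.05, adjusted for baseline. The section then says "An attrition rate of around 20% is anticipated based on our previous research" and arrives at 57 per group.
- **Secondary mental health outcomes (depression, anxiety, well-being).** By way of example, "57 participants per group is powered at 88% to observe a significant (p<0.05) main effect of group" "on baseline adjusted mental health outcomes with an effect size f=0.26".

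The planned analysis is given under Self-rated and performance-based measures: "Analysis of covariance will be calculated to estimate the effect of training condition on outcome measures after adjusting for baseline performance and grouping stratification variables". The same model is planned for the EQ and for the mental health scales. No one-sided test, baseline–outcome correlation or repeated-measures model is mentioned for either calculation.

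**The concern.** The two statements describe the same kind of test at the same significance level. Going from the first to the second, the sample rises from 90 to 114 (a factor of 1.27) but f² falls from 0.0900 to 0.0676 (a factor of 0.75). The product falls, so power should fall slightly below 80%. The plan says that it rises to 88%.

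The second statement also uses all 114 randomised participants, although the section has just treated about a fifth of them as likely to be lost.

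This is the only power figure given for depression, anxiety and well-being, which are the subject of research question 2a. Anyone interpreting a null result on the CES-D or RCADS, or planning a later trial from these estimates, would believe that an effect of f=0.26 had a 12% chance of being missed.

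**Working it through.** **Inputs, all from the Sample size section unless noted**

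- Mental health outcomes: N = 2 × 57 = 114, f = 0.26, p<0.05, main effect of group, baseline adjusted; stated power 88%.
- Primary outcome: N = 90, f = 0.3, α = 0.05, baseline adjusted; stated power 80%.
- Attrition of about 20%: 114 × 0.8 = 91.2, so 91 to 92 completers.
- Model: baseline-adjusted ANCOVA (Self-rated and performance-based measures).

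**Formula.** For two groups and one covariate, in the G*Power convention, the F statistic has df1 = 1, df2 = N − 3 and noncentrality λ = f² × N. Power is the probability that a noncentral F with these parameters exceeds the central 95% point. An F test of a group main effect is non-directional.

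**Step 1: reproduce the primary figure.** λ = 0.3² × 90 = 8.10, df2 = 87, power = 80.4%. The stated 80% is reproduced, which fixes the convention.

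**Step 2: mental health outcomes, no dropout.** λ = 0.26² × 114 = 7.71, df2 = 111, power = 78.6%. With no covariate or with three (to allow for the stratification variables), it is still 78.6%. A normal approximation with d = 2f = 0.52 gives 79.3%.

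**Step 3: after 20% attrition.** At N = 91, λ = 0.26² × 91 = 6.15 and power = 68.9%. At N = 92 it is 69.4%.

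**Step 4: what 88% would require**

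| Fixed | Solved for | Result |
|---|---|---|
| f = 0.26, power 88% | analysed N | 148 |
| N = 114, power 88% | f | 0.296 |
| N = 114, f = 0.30 | power | 88.8% |
| N = 91, power 80% | f | 0.297 |

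**Step 5: unstated assumptions that might explain 88%.** Each is applied to both claims, since the section uses one approach.

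| Assumption | Mental health claim (stated 88%) | Primary claim (stated 80%) |
|---|---|---|
| Two-sided ANCOVA, f as given | 78.6% | 80.4% |
| One-sided 5% | 86.7% | 88.1% |
| f on the unadjusted scale, baseline correlation 0.5 | 88.8% | 90.1% |
| Between-group test on 2 repeated measures, correlation 0.5 | 88.8% | 90.2% |

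For the third row, the adjusted effect is f/√(1 − r²): 0.26/√0.75 = 0.300 and 0.3/√0.75 = 0.346. For the fourth, λ = f²N × 2/(1 + 0.5): 10.28 and 10.80. In every row the mental health claim comes out below the primary claim, as it must while 7.71 < 8.10. No row gives 88% and 80% together.

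**The case against.** The best defence has four parts.

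1. **The figure is an illustration.** The sample size was derived from the EQ, and that derivation is sound (90/0.8 = 112.5, so 113; planned 114). For mental health outcomes the stated rationale is consistency with earlier work and useful point estimates in a feasibility trial. This stands: the error does not touch enrolment or the primary analysis. It does not make the printed number right.

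2. **An unstated assumption may lie behind 88%.** If f=0.26 is on the unadjusted scale, a baseline correlation of about 0.48 gives 88.0%. This is possible, but the sentence attaches f=0.26 to baseline-adjusted outcomes, no correlation is given, and the same correlation would lift the primary figure to about 89%. A repeated-measures test is not the planned analysis. At most, the authors would have an assumption to disclose, and the sentence would still need changing. Likewise, f=0.30 in place of 0.26 is a possible source of the number, but it cannot be shown to be the source.

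3. **The attrition figure is pessimistic.** The sentence is explicitly about 57 per group, and the plan is intention-to-treat with imputation and a mid-intervention measurement. The 69% does assume that those lost contribute nothing, and should be labelled so. Imputation under missing at random may recover part of that loss but does not restore the full-sample information, and even full retention gives only 79%. The favourable readings in step 5 also drop to about 79% (one-sided) and 81% (correlation 0.5) at 91 completers.

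4. **The 12% miss risk applies only if the true effect is f=0.26.** True, and the corrected 21% to 31% carries the same condition.

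**Conclusion.** The stated power is wrong for its stated inputs. At f=0.26 and a 5% non-directional test, 57 per group gives 78.6% power with complete data. With 20% attrition and no information from lost participants it is 68.9% (91 completers) to 69.4% (92). The type II error is 21% to 31% against the implied 12%. The inconsistency with the 80% primary figure holds under any single convention, because it depends only on the ordering of f² × N. The primary calculation and the planned enrolment are unaffected.

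**What to change.** Replace the sentence with one to this effect: 57 per group gives 79% power at f=0.26 if there is no dropout, and 69% if 20% are lost and contribute no information; with about 91 completers the effect detectable with 80% power is f=0.30. If the authors did use a further assumption, such as a baseline correlation, they should state it and apply it to both power calculations.

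The cost is one sentence and a less favourable figure. Sample size, outcomes and analysis stay as they are.

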### Intervention

#### Decentering training

A 5-week psychological decentering training programme was developed by [name], [name] and TD, based on our previous protocol.^28^ This involves audio-recorded scripts and an accompanying work book that guides participants through four types of decentering techniques; this structure is partly based on a recent taxonomy of self-distancing (a construct closely related to decentering).^29^ The decentering techniques include: (week 1) *spatial distancing* wherein individuals are taught to reimagine negative memories from a physically distant perspective (eg, ‘replay the memory but as if you’re a fly on the wall’); (week 2) *verbal distancing/cognitive defusion* wherein individuals are taught to rephrase negative self-relevant statements in a way that challenges its literal value and influence over affective behaviour (eg, replacing first person pronouns with one’s name); (week 3) *temporal distancing* wherein individuals are taught to reconsider specific worries from a temporally distant future (eg, ‘how would this seem in 5 years?’); and (week 4) *objective distancing* wherein individuals are taught to adopt a third-person perspective towards negative memories (eg, ‘what is the effect of reliving a difficult memory from the perspective of an objective observer?). Week 5 is a revision week, during which participants will be encouraged to practice a different technique from weeks 1 to 4 each day. These techniques were selected since they are directly targeted at how adolescents relate to and observe day-to-day psychological stressors. Specifically, the goal is to teach adolescents concrete ways to generate an objective (or distanced) self-perspective in response to everyday feelings, thoughts and memories that are unpleasant. We assume this training will develop participants’ decentering ability above their baseline levels.

Each week will involve 5 audio-recorded exercises (10–15 min) that will be made available using common streaming services. One exercise will be posted each weekday, Monday to Friday. The first two exercises (Monday and Tuesday) are brief mindfulness grounding exercises designed to promote open monitoring of psychological experiences. The next three exercises (Wednesday to Friday) are decentering training exercises as described above. Adherence to the programme will be encouraged by directly contacting the participants prior to week 1 and at week 3 to discuss their experiences so far and allow troubleshooting. Participant engagement will be monitored by reviewing the number of completed workbook exercises at the end of the 5 weeks. Participants will also complete daily diaries. These will include five questions about the intervention and its application, such as ‘Did you complete any of the programme exercises today?’ or ‘During the day, were you able to apply the skills you've learned from the exercises?’ (see online supplemental appendix A). A participant’s engagement in the trial will be discontinued if they elect to withdraw their participation or if they experience serious physical/mental health difficulties that necessitate medical or psychological intervention.

10.1136/bmjopen-2021-056864.supp1Supplementary data

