#### Participant retention and follow-up

Retention will be promoted in a number of ways. First, participants will not be paid until receipt of their completed postintervention assessment battery. Second, participants will be made aware that they can receive a bonus payment of £20 if they complete all of their assessments and daily diaries. Third, telephone contact will be made with participants prior to week 1 and during week 3 to allow any troubleshooting and ensure that participants are filling in diaries and experience sampling appropriately. Telephone contact will also be made with a participant should they fail to complete mid-intervention assessments (week 3).

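### Serious health difficulty ends trial participation, not just the programme, and nothing provides for outcome collection afterwards, although the analysis is intention-to-treat under missing at random

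*Protocol article*

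**What the plan says.** All references are to the protocol article.

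- **Discontinuation** (Intervention, Decentering training). The sentence opens "A participant’s engagement in the trial will be discontinued if they elect to withdraw their participation" and continues "or if they experience serious physical/mental health difficulties that necessitate medical or psychological intervention". What ends is engagement in the trial. The rule is not repeated under Physical and cognitive exercise, but its wording reads as covering both arms.
- **Follow-up after discontinuation.** No section says whether mid- or post-intervention inventories are still sought from someone who has been discontinued.
- **Analysis** (Self-rated and performance-based measures). "The analysis will be conducted on an intention-to-treat basis". The primary endpoint is post-intervention EQ adjusted for baseline. On missing data: "We will assume that data will be missing at random and address this using standard imputation approaches in R".
- **Payment.** The participants section attaches £100 in vouchers to finishing the five weeks of training and £20 to completing all assessments. Participant retention and follow-up adds the daily diaries to the conditions for the £20 and says that "participants will not be paid until receipt of their completed postintervention assessment battery".
- **Chasing missed assessments** (same section). A call after a missed assessment is stated for mid-intervention only.

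**The concern.** An intention-to-treat comparison needs outcomes from everyone randomised as far as they can be obtained. A rule that removes people from the trial because their health has worsened creates missing outcomes by design, and the reason for the loss is related to what is being measured. Entry requires a CES-D score of 16 or more, so mental health difficulties during the trial are a realistic possibility.

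The link is closest for the secondary outcomes: CES-D, RCADS and WEMWBS measure the state that triggers the exit. For the primary EQ the link is indirect. The Background reports that adolescents with higher self-reported decentering have fewer anxiety and depression symptoms, so those who leave for mental health reasons may also differ on EQ.

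The payment terms may add to the loss. Someone who stops training appears to forfeit the £100 and has at most £20 of the £120 left as a reason to return the post-intervention battery.

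This is a matter of design. An analysis plan can add sensitivity analyses, but it cannot recover questionnaires that were never sent.

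**Working it through.** **1. The plan's own figures.** Inputs from Sample size: total N = 90, f = 0.3, α = 0.05, one baseline covariate, about 20% attrition, 57 per group.

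- ANCOVA F test with noncentrality N·f² = 90 × 0.09 = 8.1 and 1 and 87 degrees of freedom: power 80.4%. N = 90 is the smallest total that reaches 80%.
- Attrition: 45 / (1 − 0.20) = 56.25, rounded up to 57 per group.
- For two equal groups d = 2f = 0.60 adjusted SD.

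The stated sample size reproduces. The inflation replaces lost numbers and so protects power. It does nothing about bias from who is lost.

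**2. Bias formula.** Let m be the proportion of an arm with a missing outcome, and δ the amount by which the true mean of those missing lies below the value imputed under missing at random, in adjusted SD. Then

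bias in (decentering − control) = m_T·δ_T − m_C·δ_C.

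The documents give neither the rate of health-related discontinuation nor δ, so what follows is illustration under stated assumptions.

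**3. EQ, loss that matters in one arm only.**

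| Assumed loss in that arm | Assumed δ | Bias | Share of 0.60 SD |
|---|---|---|---|
| 3 of 57 (5.3%) | 0.5 SD | 3/57 × 0.5 = 0.026 SD | 4% |
| 20% | 0.25 SD | 0.20 × 0.25 = 0.05 SD | 8% |
| 20% | 0.5 SD | 0.20 × 0.5 = 0.10 SD | 17% |
| 20% | 1.0 SD | 0.20 × 1.0 = 0.20 SD | 33% |

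The first row represents a few health-related exits. The others treat all the anticipated attrition as informative, which is an extreme use of the 20%.

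**4. EQ, loss in both arms.** With 20% missing and the same δ in each arm, the bias is 0.20δ − 0.20δ = 0. With 30% against 10% and a common δ of 0.5 SD, it is (0.30 − 0.10) × 0.5 = 0.10 SD. The sign follows the arm with the heavier or worse loss.

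**5. CES-D.** If 3 of 57 in one arm are missing with true scores 10 points worse than imputed, that arm's mean is too favourable by 3/57 × 10 = 0.53 points.

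**The case against.** Several objections carry weight.

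- **The wording is open.** The same section uses engagement for completed workbook exercises, so the rule could be meant for the programme alone. The article is also a condensed account. But the sentence names the trial, and nothing in the article points to continued assessment. At the least, the two readings need to be separated.
- **Missing at random is not contradicted.** A reader might infer that the rule makes the assumption false. It does not follow. The assumption allows missingness to depend on observed data, and the plan collects baseline and mid-intervention inventories plus experience sampling four times a day. Deterioration may show there before exit, and imputation using those data could make the assumption approximately true. The imputation variables may be given in an analysis plan that is not shown, so they are not counted against this one. The assumption is weakest where deterioration comes after the last completed measure.
- **The primary outcome is not a health measure.** A reader might infer that the primary endpoint goes missing for those doing worst. EQ is primary and depression and anxiety are secondary, so the effect on EQ rests on a reported association.
- **The direction is unknown.** A reader might infer that decentering training would look better than it is. That needs heavier or worse loss in the decentering arm, and the documents do not establish it.
- **Payment also supports retention.** Nothing is paid until the post-intervention battery arrives, there is a separate £20 for assessments, and calls are made before week 1 and in week 3. These help among those who finish training. The incentive for those who stop remains weak on the stated terms, although no completion threshold or part-payment rule is given.

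**Conclusion.** The point holds as a design weakness of moderate weight. As written, the rule ends trial participation for a health-related reason without provision for later outcomes, in a trial that promises an intention-to-treat analysis. The secondary mental health outcomes are the most exposed, and the primary EQ possibly.

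With a 0.5 SD gap in one arm only, the EQ bias runs from about 0.03 SD (3 of 57 lost) to 0.10 SD (20% lost), or 4% to 17% of the 0.60 SD design effect. Both the loss and the gap are assumed. Equal loss with equal gaps gives no bias, and unequal loss could push the estimate either way. The documents do not support a claim that the trial's result will be biased, or biased in favour of decentering. They do support the narrower conclusion that outcomes which could be collected would be lost, leaving more of the result dependent on an assumption the data cannot test. The payment terms are a possible contributor and do not carry the point alone.

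**What to change.** Leave the investigators' rule for stopping the programme unchanged. Add that stopping the programme does not by itself end outcome assessment. Unless consent is withdrawn or the investigator judges contact inappropriate, participants should still be invited to the online mid- and post-intervention inventories, at least the EQ and the main mental health scales, and be analysed in the group to which they were randomised. Record the reason and date for each discontinuation by arm, so that the loss can be described.

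The cost is an ethics amendment and revised consent wording. The Blinding section says that all outcomes are completed online through the same link in both groups, so no new infrastructure is needed.

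Optionally, part of the existing payment could depend on the post-intervention battery whether or not training was finished. The total would not change, but the incentive to complete training would be weaker, so this is for the sponsor to weigh.
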